#### Interim analyses {21b}

There will be no interim analysis.

#### Methods for additional analyses (e.g., subgroup analyses) {20b}

In addition to the primary analysis, we will perform subgroup analyses to examine potential differences between subsets of participants. We will analyze subgroups according to the following characteristics: maternal age (<25 compared to ≥25), primiparous or multiparous, education (less than high school versus high school or more), adult attachment style (ECR-S), single parent or cohabiting, initial trauma level (above cutoff or not on subscales), the initial level of reflective function (lowest 50% versus highest 50%), the initial level of depression or anxiety (clinical or not-clinical level), financial strain (report bad economy or high worry about the economy), and attendance (dose).

We will also examine whether there are differential effects concerning two different composite variables where we combine some of the abovementioned variables: (1) Social determinants of health (based on poverty, low levels of education, single parenthood, and low maternal age); and (2) Low psychological resources (based on depression, anxiety or trauma experience).

For attendance, we will examine if there are differential effects concerning (1) the number of sessions, (2) parents who have participated in the MTB intervention until the child is 1 year old, and (3) light participation (<45 sessions), planned participation (45–90 sessions), and heavy participation (more than 90 sessions).

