#### Baseline measures

In addition to the socio-demographic measures, we include the following measures at baseline to assess the initial level and to account for them as possible moderators or confounders in the effect analyses.

The Prenatal Parental Reflective Functioning Questionnaire (P-PRFQ) [76] is a 14-item measure of *parental reflective functioning* or the pregnant woman’s ability to mentalize. The P-PRFQ is an adaptation of the PRFQ [77] and consists of three subscales: opacity of mental states (4 items), reflecting on the fetus-baby (5 items), and the dynamic nature of mental states (5 items). Cronbach’s alpha is 0.77 for the total score and 0.69–0.77 for the three subscales. Responses are on a Likert scale ranging from 1 to 7 with three different scales: (1) High-Low where 7 = optimal PRF, 1 = low PRF; (2) Low-High where 1 = optimal PRF, 7 = low PRF, and (3) Middle where 4 = optimal PRF, 1 and 7 = low PRF. The total score range is 7–98.

The Hospital Anxiety and Depression Scale (HADS) [78, 79] is a 14-item measure of *anxiety and depression*. HADS consists of the two subscales “anxiety” and “depression,” both ranging from 0 to 21, where low scores indicate less anxiety and depression.

The Experiences in Close Relationship Scale-Short Form (ECR-S) [80] is a 12-item measure of *adult attachment* consisting of the two subscales: “Anxiety” (fear of abandonment and a craving for interpersonal closeness) and “avoidance” (fear of intimacy and interpersonal dependency). Each subscale ranges from 1 to 42, where low scores indicate better attachment.

The Childhood Trauma Questionnaire (CTQ) [81] is a 28-item measure of adverse childhood experiences (ACE). Items are rated on a 5-point Likert scale (Never true, Rarely true, Sometimes true, Often true, Very often true). The CTQ consists of five subscales: emotional abuse, physical abuse, sexual abuse, emotional neglect, physical neglect, and a minimization/denial subscale. Each subscale ranges from 5 to 25, where low scores indicate less trauma experience.

The PTSD-8 inventory [82] is an 8-item measure of *posttraumatic stress disorder (PTSD) symptoms*, including intrusion, avoidance, and hypervigilance. The total score range is 8–32, where a low score indicates a lower level of PTSD.

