### Sample size {14}

Power analysis was carried out in the design phase to assess the statistical power for testing the main hypothesis. The power calculation is based on a meta-analysis of interventions aimed at improving parenting sensitivity [57]. The overall average effect size was 0.44 (standardized mean difference, SMD). We expect controls to constitute about one-third of the sample. For normally distributed outcomes and using a two-sided alpha of 0.05, and a beta of 80%, we would need a total of 183 participants (61 control and 122 intervention) for an effect size of 0.44 SMD. To leave room for dropout, we plan to recruit 250 participants (75 control and 175 intervention).

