### Statistical methods

#### Statistical methods for primary and secondary outcomes {20a}

The treatment effect of MTB relative to CAU on the primary outcome (parental sensitivity at child age 12 and 24 months) is analyzed as the mean change from baseline to post-intervention using ordinary least squares regressions separately. The analysis will be adjusted for stratification variables (municipality) and the baseline value of the outcome variable. Variables with indications (*p* < 0.1) of differences between intervention and CAU groups at baseline are also used as control variables. The treatment effect is estimated as a fixed effect using a binary indicator of MTB treatment, and cluster-robust standard errors based on wild bootstrap are used for inference. We evaluate the longitudinal effects separately for the 12-month and 24-month measurements. Two-sided tests with 0.05 significance levels are applied throughout. Analyses of secondary outcomes will be conducted analogously with follow-up analysis at child age 3 months in addition.

Additional exploratory analyses will be carried out in a generalized linear mixed models framework permitting the estimation of flexible nonlinear time patterns to examine the potential heterogeneity of treatment effect sizes across follow-up points.

To avoid the inflation of type 1 error due to multiple outcomes being tested simultaneously, we calculate the false discovery rate (FDR) on the secondary outcomes. In addition, we perform a sensitivity analysis using a Seeming Unrelated Regression framework to collectively examine treatment across all primary and secondary outcomes at age 12-month and 24-month follow-up, hence accounting for the covariance of outcomes.

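### Baseline reflective functioning is examined as an effect modifier only as a median split, which loses about 36% of the information if the score is roughly normal and the gradient linear

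*Protocol article*

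**What the plan says.** Under the protocol article's section on additional analyses {20b}, "we will perform subgroup analyses to examine potential differences between subsets of participants". One of the ten listed characteristics is "the initial level of reflective function (lowest 50% versus highest 50" per cent. No external norm is cited, so the natural reading is a cut at this sample's own median.

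The section Baseline measures says that the P-PRFQ "is a 14-item measure of" reflective functioning, with items answered from 1 to 7, and that the baseline instruments are collected "to account for them as possible moderators or confounders in the effect analyses". It gives no functional form for that role.

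The Statistical methods section {20a} plans adjusted ordinary least squares for the outcomes and adds: "Two-sided tests with 0.05 significance levels are applied throughout". The Sample size section {14} addresses the main effect only. No power, effect size or score distribution is given for any subgroup comparison.

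**The concern.** A many-valued score is reduced to two groups. Mothers just below and just above the median are treated as different, while a mother near the median and one at the extreme of the same half are treated as alike. If the benefit of MTB changes gradually with initial reflective capacity, the contrast between halves uses only part of the evidence for that change.

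The cut also stands apart from most others in the same list. Age (25 years), education (high school), trauma (a cutoff) and depression or anxiety (a clinical level) rest on boundaries that exist outside the sample, and attendance is also examined as a number of sessions. The boundary for reflective functioning will be whatever median this sample yields, so the estimates for the two halves cannot readily be carried to another municipality or trial.

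Reflective functioning is a central target of MTB, so whether the effect depends on its starting level is of real interest. What is at stake is the sensitivity and portability of that one additional analysis.

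**Working it through.** **Inputs from the Sample size section {14}.** "The overall average effect size was 0.44 (standardized mean difference, SMD"), so the outcome SD is 1; controls are about one-third of the sample; the calculation is done "using a two-sided alpha of 0.05, and a beta of 80" per cent (read as 80% power); 183 mothers are needed, 61 control and 122 intervention.

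**Step 1: the plan's own figure.** Controls needed at 1:2 allocation = (1 + 1/2) × (1.960 + 0.842)² / 0.44² = 1.5 × 7.849 / 0.1936 = 60.8, so 61, and 3 × 61 = 183. The stated figure is reproduced.

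**Step 2: information kept by the split.** Take a standard normal score X and G = 1 when X is above the median. Then cov(X, G) = 1/√(2π) = 0.399 and SD(G) = 0.5, so the correlation is 0.798 and its square is 2/π = 0.637. For a linear gradient, 36.3% of the information is lost. Recovering it would need 1/0.637 = 1.57 times the sample.

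**Step 3: other score shapes (assumed, because the documents give no distribution).** The loss is 25% for a uniform score and 48% for a skewed one (log-normal, sigma 0.5).

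**Step 4: power for the interaction.** With the score in SD units and residual SD 1, the SE of the interaction slope is 1/√(N·p·(1−p)) = 1/√(183 × 1/3 × 2/3) = 0.157. The z for the continuous score is gradient/SE, and the z for the split is 0.798 times that. Power = Φ(z − 1.96) + Φ(−z − 1.96). The gradients are assumptions: the change in MTB effect, in outcome SDs, per SD of P-PRFQ.

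| Gradient | z, continuous | z, split | Power, continuous | Power, split | Loss (points) |
|---|---|---|---|---|---|
| 0.10 | 0.64 | 0.51 | 9.8% | 8.0% | about 2 |
| 0.22 | 1.40 | 1.12 | 28.9% | 20.1% | about 9 |
| 0.30 | 1.91 | 1.53 | 48.1% | 33.3% | about 15 |
| 0.44 | 2.81 | 2.24 | 80.1% | 61.0% | about 19 |

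With all 250 planned mothers analysed (75 and 175) and a gradient of 0.22, power is 35.7% against 24.6%, a loss of 11 points.

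**Step 5: simulation check.** OLS with 4,000 runs at N = 183 gave 77.7% against 56.9% at a gradient of 0.44, and 27.1% against 18.7% at 0.22. Levels are a little lower than the formula gives, and the losses are of the same size.

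**Step 6: where the loss peaks.** Under normality the largest possible loss is 19.4 points, when the continuous test has about 75% power. From an 80% starting point, the loss is 12 points for the uniform score and 28 for the skewed one.

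All figures assume individual-level OLS. Clustering and the wild bootstrap are left out; they would lower power for both forms.

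**The case against.** The strongest case is that little depends on this. It is one of ten subgroup variables plus two composites, outside the primary analysis. No P-PRFQ cutoff is given in the documents, and a median fixed in advance at least prevents choosing a cutpoint after seeing the results. For modest gradients both forms are badly underpowered, so the split is not the main reason a gradient would be missed. Linearity is not obvious either: Baseline measures describes three scoring directions, one of them with the midpoint as optimum. If the truth were a step at the median, the split would lose nothing, and the linear term would be the one keeping only 64%, because the squared correlation is symmetric. The section also does not say whether the halves will be compared through an interaction term, which the calculations assume. These points stand; they limit the size of the finding. They do not justify making the halves the only form, because the documents give no reason to expect a step at the median.

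Two stronger readings are tempting and should be resisted.

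- A reader might infer that the split costs this trial nearly 20 points of power. That needs a gradient of about 0.44 SD per SD, as large as the whole assumed main effect. MTB would then have an effect of 0.44 − 0.44 = 0 at one SD to one side of the mean score and 0.44 + 0.44 = 0.88 at one SD to the other, or 2 × 0.798 × 0.44 = 0.70 between the halves. Nothing in the documents supports a modifier of that size.
- A reader might infer from Background and rationale {6a} that mothers at highest risk gained most in the first US trial. The text says only that they improved in reflective functioning. It makes no such comparison, does not define high risk as low initial reflective functioning, and treats reflective functioning as an outcome, not as a modifier of the effect on sensitivity.

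**Conclusion.** The point holds in a limited, conditional form. The article fixes a median split as the only stated way to examine baseline reflective functioning as a modifier, although a many-valued score will be available. The information loss is about 36% for a roughly normal score and a linear gradient, and 25% to 48% under the other distributions tried. The power cost depends on a gradient that the documents do not give: 80% falls to about 61% at 0.44 SD per SD, with losses of about 9 points at 0.22 and about 2 points at 0.10 (N = 183), and none for a step at the median. The cut's dependence on the enrolled sample does not rest on these assumptions. No primary or secondary estimate is affected, so this is a worthwhile refinement and not a flaw in the trial's main inference.

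**What to change.** Before outcome data are analysed, state in the analysis plan that moderation by baseline reflective functioning is tested with a treatment-by-continuous P-PRFQ interaction, in the same adjusted OLS model and with the same inference as in {20a}. Check linearity with a quadratic or spline term. Report the estimated MTB effect with its confidence interval at a few chosen score values; stated scores travel better than sample percentiles, which are themselves tied to who enrols. Keep the lower-half and upper-half estimates for display.

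The cost is a sentence or two and no new data. The downside is the linearity assumption, which the added term checks, though with limited power at this sample size.

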#### Methods in analysis to handle protocol non-adherence and any statistical methods to handle missing data {20c}

The primary analysis will be based on the intention-to-treat (ITT) principle, aiming to include all participants in the arm they were originally allocated to irrespective of the amount of treatment received. Missing data is handled using multiple imputations using all available baseline data. Sensitivity analyses will be performed to investigate the potential impact of missing data, in particular by using a pre-specified conservative multiple imputation strategy and a complete case analysis.

#### Plans to give access to the full protocol, participant-level data, and statistical code {31c}

To protect participant privacy, the de-identified datasets generated and analyzed during the current study will not be publicly available, but will be available from the corresponding author on reasonable request.

### Oversight and monitoring

#### Composition of the coordinating center and trial steering committee {5d}

VIVE will monitor the study to ensure adherence to ethical aspects, participant rights, and quality of data documentation. The first author (MP) is the primary investigator (PI) and project manager. Day-to-day support is provided by MP, MFH, the trial statistician MT, and a research assistant. The trial does not have a trial steering committee.

#### Composition of the data monitoring committee, its role and reporting structure {21a}

Adverse effects of the intervention are not anticipated; thus, no data monitoring committee is needed in this study.

#### Adverse event reporting and harms {22}

Based on previous studies, we do not anticipate and adverse events. However, if any adverse events occur, they will be reported to the Institutional Review Board at VIVE.

#### Frequency and plans for auditing trial conduct {23}

During the study, the PI meets with each municipality to monitor participant safety and data assessment procedures. The project management group meets monthly to review trial conduct.

#### Plans for communicating important protocol amendments to relevant parties (e.g., trial participants, ethical committees) {25}

If there would be any further necessary protocol amendments a revised copy will be stored and the protocol in the clinical trial registry will be updated. Any amendments or changes will also be transparently described in the publications following the trial.

#### Dissemination plans {31a}

Results will be published in peer-reviewed journals of general and special interest and presented at international conferences. Authorship will follow the Vancouver guidelines. To disseminate the results beyond the scientific community, we will write Danish reports aimed at practitioners and policymakers and present results at the VIVE webpage and through social media platforms.

## Discussion

This paper describes the protocol for a quasi-cluster-randomized controlled trial that aims to examine the effects of the Minding the Baby® home visiting intervention offered to pregnant women at increased risk of adversity on parental sensitivity, parent-child interaction, parental reflective functioning, parental mental health, maternal satisfaction, parental stress, and child development and well-being. This study will provide knowledge on how the MTB intervention works in a Scandinavian context and how to best support families with complex problems in pregnancy and the first years of life. The study will include the largest sample of MTB families to date, increasing the power of the study to detect differences between intervention and control families.

The Scandinavian countries are characterized by universal access to a wide selection of services for all of its citizens (including free and universal health care, birth preparation, generous parental leave, subsidized universal daycare, attractive ratios of children to caregiving staff, free access to schooling and education) [107]. The emphasis on preventive care and existing health and mental health infrastructure in Danish municipalities allow for implementation and potential sustainability of programs such as MTB. This study is the first study implementing MTB in a Scandinavian welfare context and therefore provides important knowledge about the transportability of the MTB intervention. If MTB is shown to be effective, the intervention can be directly implemented into standard care in Danish municipalities.

When conducting studies on families at increased risk for adversity, problems with attendance and attrition are common and inevitable [108]. Socially disadvantaged groups are less likely to engage in interventions and are often described as a “hard to reach” population for intervention studies [109]. However, poor recruitment or retention can reduce the power of a study significantly and lead to inconclusive results and issues around the generalisability of findings if the participants become a non-random subsample of the target population [110–112]. Families at increased risk for adversity may experience challenging life circumstances and complex health and social problems and do not always trust social services and other professionals [113]. Pregnancy can be a window of opportunity for intervening because the pregnant woman usually strongly wishes to be a good mother for her child [114]. However, pregnancy can also complicate the relationship with the professionals because families at increased risk of adversity fear that their child will be removed from their care if they disclose worries or challenges.

To increase attendance and reduce attrition interventions aimed at families at increased risk of adversity must be tailored to the individual family and flexible to accommodate the needs of the study population [108]. To successfully recruit parents at increased risk of adversity, it is important to offer multiple communication channels for recruitment and data collection, to offer well-integrated services and face-to-face contact and it is crucial to plan for attrition and collect data on attendance throughout intervention delivery [108].

As the target population for MTB is at increased risk for adversity, it is not surprising that the previous studies have faced challenges with recruitment and retention. Attrition rates in the two studies by the developers of the intervention ranged from 20 to 29% at 12- and 24-month assessments [61, 63, 64]. The recent study in the UK struggled with recruitment and had to downscale the study from 200 to 150 participants due to recruitment challenges [67]. The attrition rates for the present study are 27% at 6 months, 34% at 12 months, and 35% at the 2-year assessment. These problems with recruitment and retention may make it impossible to detect intervention effects smaller than *d* = .40–.50, which would include effect sizes of potential clinical significance.

In this study, the process for recruitment and data collection has been tailored to this exact group of pregnant women to increase the chance of recruiting the planned number of participants and retaining them in the study. Currently, we have collected baseline measures for 254 participants making this study the largest study of MTB. Maternal sensitivity is the primary outcome of the study and collecting video recordings from the participants is therefore pivotal. Some women refuse to submit a video recording at child age 12 and 24 months, perhaps because they fear being judged as a parent. To collect as many videos as possible, we have developed different possible procedures for video recordings (including home visits by either a known person or by independent trial staff), recording the video by the participant without any help or recording it by zoom with trial staff) and have produced a short informational video about the video recording. We will closely monitor referral, recruitment, and retention rates through the study and accommodate procedures if needed.

The study has recruited participants from June 2018 and will continue to recruit until the end of May 2022. This is a period where several historical events have taken place and impacted the study. GDPR was introduced in Europe in May 2018 right before recruitment started with many new laws concerning processing personal data for research purposes making it difficult to produce recruitment materials. Consequently, it took longer time to finalize data agreements with several municipalities. The focus on data leaks and the importance of the GDPR also made some participants wary of handing over sensitive and personal information. The Covid-19 pandemic also has affected the trial. Since March 2019, Denmark has experienced different levels of lockdown and restrictions challenging recruitment, intervention, and outcome assessment. Furthermore, Denmark experienced a strike among nurses from June 19 to August 28, 2021, where some of the health nurses were affected.

In sum, there is a need for early interdisciplinary interventions for parents and infants at increased risk for adversity. The present study of MTB in a Scandinavian context has the potential to improve the well-being of parents and infants at increased risk for adversity and to prevent health inequalities in the long run.

### Trial status

This protocol is version 1.4. Recruitment started on May 28th, 2018, and is expected to be completed in May 2022.

